### Statistical analysis

Primary analyses will be undertaken within an intent-to-treat framework, retaining all participants as randomised, regardless of extent of engagement with training or withdrawal from the study. Likelihood based methods (mixed-model repeated measures (MMRM)) will be used to assess significance of change in the two primary manager outcome measures. Clustering will be accommodated by a random cluster membership (work site) factor. A priori planned comparisons of change from baseline to the 4-month endpoint will test the primary hypothesis. An unstructured variance-covariance matrix will be used to accommodate relationships between observations at different occasions of measurement. Stratification variables and any variables found to be substantially imbalanced between intervention arms post randomisation will be tentatively included in these models and retained if statistically significant and influential on outcomes. Length of time from baseline to complete training and associated post-intervention assessment will also be introduced tentatively into models to evaluate the effects of adjustment for possible effects associated with some managers undertaking these assessments earlier than others and earlier than control group participants.

Similar analyses of scaled secondary manager outcomes will assess differential change due to intervention arm. Mathematical transformation or categorisation of raw scores may be undertaken to meet distributional assumptions and address any violation of assumptions attributable to outliers. Comparable analyses of employee measures will additionally accommodate the nesting of employees within managers by including a random effect for managers where this is possible.

Additional per-protocol analyses to assess effectiveness of the program will focus on managers who completed at least one of the three topics. This subgroup will be compared to all responders in the waitlist control group and, secondarily, with managers who completed less of the training material. The latter comparison will inform the dose-response profile of the intervention and, in particular, whether completing only a subset of the earlier components of *HeadCoach* has a benefit comparable to the complete program.

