All tests of treatment effects will be conducted using a two-sided alpha level of 0.05 and 95% confidence intervals. A member of the research team who is blinded to the intervention and waitlist control allocations will perform this analysis. The nature of the intervention will make blinding managers to their group allocation impossible.

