### Sample size and power calculations

Our industry partners comprise a total of 42 geographical clusters with an average of 20 managers in each cluster. Participation in this study will be voluntary. Based on pilot data, we assume a conservative participation rate of 20% of all managers, with a drop-out rate of 25%. Based on these assumptions, we anticipate being able to recruit a minimum of 168 managers and to successfully follow up 126. Assuming an intraclass correlation of 0.05 yields a design effect of 1.15, the forecast achievable sample size would have 80% power to detect a moderate effect size of 0.54 using an alpha value of 0.05.

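### The within-arm comparison meant to inform whether a partial HeadCoach course is comparable to the full one cannot answer that question: it does not contrast partial with full completers, and nothing stated gives a basis for calling them comparable

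*Protocol article*

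**What the plan says.** The Statistical analysis section of the protocol article adds per-protocol analyses to the intention-to-treat primary analysis. They focus on "managers who completed at least one of the three topics". Two comparisons follow: "This subgroup will be compared to all responders in the waitlist control group and, secondarily, with managers who completed less of the training material". The second is described as informing how benefit varies with the amount completed. One question is singled out there, namely "whether completing only a subset of the earlier components of *HeadCoach* has a benefit comparable to the complete program".

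The inference convention comes at the end of the same section: "All tests of treatment effects will be conducted using a two-sided alpha level of 0.05 and 95% confidence intervals". The article gives no margin or other criterion for what counts as comparable.

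The Sample size and power calculations section covers only the randomised two-arm comparison: "we anticipate being able to recruit a minimum of 168 managers and to successfully follow up 126", with "80% power to detect a moderate effect size of 0.54 using an alpha value of 0.05".

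**The concern.** Whether a partial course has "has a benefit comparable to the complete program" is a question about the absence of an important loss. Two features of the plan do not fit it.

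- **The contrast.** The question sets a subset against the whole course. The stated comparison sets one or more topics against less. A manager who finished one topic and a manager who finished all three are on the same side, so the loss from stopping early is not estimated.
- **The inference.** A two-sided difference test can show that two groups differ. Failing to show it does not show that they are alike, least of all in a fraction of one arm. A confidence interval can speak to comparability, but only against a stated loss that would matter.

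What is at stake is a message about delivery. The Discussion names low completion as a known problem of eLearning, so a finding that the early topics suffice would be attractive. A null result in a small comparison could be taken that way without supporting it.

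**Working it through.** **Inputs from the article** (Sample size and power calculations): 42 clusters, 20 managers per cluster on average, 20% participation, 25% drop-out, intraclass correlation 0.05, design effect 1.15, effect size 0.54, 80% power, alpha 0.05.

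**Step 1. Reproduce the article's own figure.**
- Recruited: 42 × 20 × 0.20 = 168. Followed up: 168 × 0.75 = 126.
- Design effect: 168 / 42 = 4 managers per cluster, and 1 + (4 − 1) × 0.05 = 1.15.
- Effective number per arm: 126 / 1.15 / 2 = 54.8.
- Power for 0.54 SD, two-sided 0.05: 0.807 by the normal approximation, 0.800 by the noncentral t.

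The stated 80% reproduces. It applies to the two-arm comparison only.

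**Step 2. Assumptions for the within-arm comparison.** The article gives neither an allocation ratio nor completion rates. I assume:
- 1:1 allocation, so 126 / 2 = 63 intervention managers followed up;
- all 63 belong to either the subset group or the complete group, which is generous because some will finish less than one topic;
- illustrative splits of 32/31, 21/42 and 16/47;
- no clustering, and no confounding by who chooses to finish, both of which favour the plan.

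This is the subset-versus-complete contrast that the question requires, not the one the article describes.

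**Step 3. Formulae, in SD units.** SE = √(1/n₁ + 1/n₂). The 95% half-width is t(0.975, 61) × SE = 2.00 × SE. The chance of a non-significant result at true difference d comes from the noncentral t with 61 degrees of freedom and noncentrality d / SE. For 32/31, SE = √(1/32 + 1/31) = 0.252, the half-width is 2.00 × 0.252 = 0.50, and the noncentrality at d = 0.54 is 0.54 / 0.252 = 2.14.

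| Split | SE | 95% half-width | Non-significant if d = 0.54 (subset gives nothing) | Non-significant if d = 0.27 (subset gives half) |
|---|---|---|---|---|
| 32/31 | 0.252 | 0.50 | 44% | 82% |
| 21/42 | 0.267 | 0.53 | 49% | 83% |
| 16/47 | 0.289 | 0.58 | 55% | 85% |

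**Step 4. Less favourable assumptions.** With splits from 50:50 to 10:90 and a design effect from 1.0 to 1.15 (normal approximation), the chance of non-significance at d = 0.54 runs from 43% to 78%, and the half-width from 0.49 to 0.88 SD.

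**Step 5. Could the planned interval settle it?** This needs a margin, and the article gives none. Take 0.27 SD, half the planned effect, as an example. If the partial and full courses were truly identical, the 95% interval would exclude a loss of 0.27 SD only 15% to 18% of the time across the three splits. For 80% power at one-sided 0.025 with equal groups and no true difference, n per group = 2 × (1.960 + 0.842)² / margin²:
- margin 0.27: 216 per group, 432 in total;
- margin 0.54, the whole planned effect: 54 per group, 108 in total.

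Both exceed 63, before any allowance for clustering.

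**The case against.** The strongest reply is that the article never claims what a critic might fear. The comparison is additional, per-protocol and secondary, and it is said only to inform the question. No hypothesis or success rule is attached. A reader might infer that the plan sets out to establish equivalence and would accept a non-significant test as proof. The text supports neither inference: no sentence equates non-significance with comparability, and 95% confidence intervals are planned alongside the tests. A margin for an exploratory comparison is also detail that a condensed article may leave to an analysis plan not shown here. Finally, the 63 and the splits are assumptions, and 44% to 55% is close to a coin toss, so a null result cannot be called the expected one.

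Most of this stands, and it limits the point. It does not remove it. The mismatch between the question and the groups is in the text itself: at least one topic versus less is not subset versus complete. The phrase about completing less might be meant as a graded comparison, but the preceding sentences define only the one-topic threshold. The intervals help only when read against a loss that matters, and with a half-width near the whole planned effect they would rarely exclude even a large one. So the difficulty is not just an unstated margin: a comparison of this size has little prospect of answering the question at 0.27 SD, whatever an analysis plan adds.

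**Conclusion.** The point holds in a limited form. The article gives a secondary, non-randomised comparison a comparability question that its stated groups do not address and its stated inference cannot support. Even with the groups redrawn, a subset course giving none of the planned 0.54 SD benefit would be non-significant about 44% to 55% of the time, with a 95% half-width of about 0.50 to 0.58 SD. These figures rest on 1:1 allocation, 63 intervention managers followed up, illustrative splits, no clustering and no confounding. The intention-to-treat primary analysis and its power statement are not touched. The article commits to no false conclusion, but it offers no sound basis for the word comparable.

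**What to change.** In the per-protocol paragraph of the Statistical analysis section:

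1. Define the contrast as managers who completed only a subset of the topics versus those who completed all three.
2. Report the difference in confidence change with its 95% confidence interval, labelled exploratory and non-randomised, because managers choose how much to complete.
3. State that a non-significant difference will not be read as comparable benefit.
4. Either use the word comparable only if the interval excludes a loss larger than a margin fixed before unblinding, and otherwise report the result as inconclusive, or drop the comparability aim and describe the dose-response pattern only. The 0.27 SD used above is an illustration; the investigators should choose and justify the margin.

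The cost is a few sentences, with no extra data or participants. The downside is that the trial will probably be unable to say that a partial course suffices.

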### Sample size and power calculations

Our industry partners comprise a total of 42 geographical clusters with an average of 20 managers in each cluster. Participation in this study will be voluntary. Based on pilot data, we assume a conservative participation rate of 20% of all managers, with a drop-out rate of 25%. Based on these assumptions, we anticipate being able to recruit a minimum of 168 managers and to successfully follow up 126. Assuming an intraclass correlation of 0.05 yields a design effect of 1.15, the forecast achievable sample size would have 80% power to detect a moderate effect size of 0.54 using an alpha value of 0.05.

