**Methods/Design:**

We will conduct a cluster randomised control trial (RCT) to evaluate the effect of *HeadCoach*, an online training intervention for managers with a focus on the mental health of their employees, compared to a waitlist control. The target sample is 168 managers, and their direct employees. Managers and employees will be assessed at baseline and at 4-month follow up. Managers will have an additional, intermediate assessment 6-weeks post-baseline. The primary outcome is change from baseline in managers’ self-reported confidence when dealing with mental health issues within their team and promoting a mentally healthy workplace. The difference between the intervention and waitlist control groups will be assessed using linear mixed effects repeated measures (MMRM) analysis of variance (ANOVA). Secondary managerial outcomes include mental health literacy, attitudes towards mental health issues in the workplace and managerial behaviour in dealing with mental health matters with their staff. Employee outcomes will be perceived level of manager support, engagement, psychological distress, and rates of sickness absence and presenteeism.

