### Participants

We aim to recruit both managers and their direct reports from three large industry partner organisations collaborating with this trial. These industry partners come from the emergency services and construction sectors. Together they have 690 managers and 9100 employees reporting directly to these managers who could potentially participate in the trial.

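### The sample size rests on 840 managers (42 zones of 20), the Participants section counts 690, and the stated recruitment and power follow from the first figure only

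*Protocol article*

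**What the plan says.** Under Sample size and power calculations, the protocol article starts from the number of zones: "Our industry partners comprise a total of 42 geographical clusters with an average of 20 managers in each cluster". It then applies two rates, taken from pilot data: "we assume a conservative participation rate of 20% of all managers, with a drop-out rate of 25" per cent. From these it concludes that "we anticipate being able to recruit a minimum of 168 managers and to successfully follow up 126". The clustering allowance is "Assuming an intraclass correlation of 0.05 yields a design effect of 1.15", and the claim for the resulting sample is "80% power to detect a moderate effect size of 0.54 using an alpha value of 0.05". The abstract carries the same number forward as the trial's target: "The target sample is 168 managers, and their direct employees".

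The Participants section describes the same three industry partners and gives a different pool: "Together they have 690 managers and 9100 employees reporting directly to these managers who could potentially participate in the trial".

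**The concern.** Forty-two zones averaging 20 managers make 840 managers; the Participants section has 690. The article neither mentions the gap of 150 nor distinguishes two populations that would account for it. It is too large for ordinary rounding: 690 managers in 42 zones is 16.4 per zone, and at 20 per zone 690 managers would fill only 34.5 zones.

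The 840 is the operative input to the calculation. The recruitment forecast, the number followed up, the design effect and the power all derive from it. If the smaller count is the right base, the stated rates give 18% fewer managers than the abstract's target, and the power statement, on which the Discussion also relies, is more favourable than the plan's own rates support.

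**Working it through.** **Inputs.** From Sample size and power calculations: 42 zones, 20 managers per zone, 20% participation, 25% drop-out, intraclass correlation (ICC) 0.05, effect size 0.54. From Statistical analysis: two-sided alpha 0.05. From Participants: 690 managers. Assumed because the article does not state them: 1:1 allocation, equal cluster sizes, outcome standardised to SD 1, and no gain in power from baseline adjustment.

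**Formulas.**
- Recruited = managers × 0.20; followed up = recruited × 0.75.
- Design effect = 1 + (m − 1) × ICC, where m is participating managers per zone.
- Effective n per arm = followed up / design effect / 2.
- Power for a two-sample comparison of means, by the normal approximation and by the noncentral t.
- Detectable effect at 80% power (normal) = (1.96 + 0.84) × √(2 / effective n per arm).

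**Step 1: reproduce the plan's figures from 840.**
- 42 × 20 = 840; 840 × 0.20 = 168; 168 × 0.75 = 126.
- m = 168/42 = 4, so the design effect is 1 + 3 × 0.05 = 1.15.
- 126/1.15 = 109.6 effective, or 54.8 per arm.
- Power at 0.54 is 80.7% (normal) or 80.0% (t); the detectable effect is 0.535 (normal) or 0.540 (t).
- In reverse: 54 per arm × 2 × 1.15 = 124.2, rounded up to 125, and 125/0.75 rounds up to 167, next to the stated 168.

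Every stated figure is reproduced.

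**Step 2: replace 840 by 690 and change nothing else.**
- 690/42 = 16.4 managers per zone.
- 690 × 0.20 = 138 recruited, and 138/168 = 0.82, so 18% fewer.
- 138 × 0.75 = 103.5, about 103 followed up (103.5 is carried forward below).

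| Design effect used | Effective n per arm | Power at 0.54, normal / t | Detectable effect, normal |
|---|---|---|---|
| 1.15, kept as stated | 45.0 | 72.6% / 71.7% | 0.591 |
| 1.114, from m = 138/42 = 3.29 recruited per zone | 46.4 | 74.0% / 73.1% | 0.581 |
| 1.073, from m = 103.5/42 = 2.46 followed up per zone | 48.2 | 75.5% / 74.7% | 0.571 |

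The middle row uses the plan's own convention, since 1.15 comes from the 4 managers recruited per zone. Its detectable effect by the t calculation is 0.588. The third row counts only managers followed up; on that convention 840 gives a design effect of 1.10 and power of 82.4% / 81.7%, so the loss is of similar size.

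**Step 3: what 168 requires from 690.** 168/690 = 24.3% participation. At 168 recruited and 126 followed up, Step 1 applies again and the stated power stands.

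**The case against.** The strongest reply is that the sample size paragraph contains no arithmetic error. That is correct: a reader might infer that 168, 126 and 80% are miscalculated, but each follows from the inputs in that section. The conflict is between two sections.

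The two counts may also describe different populations. The 690 are managers who could take part; the article does not say that no others exist. Managers must supervise at least three employees, and the invitation goes to a certain management level, so 840 could be all managers and 690 the eligible ones. The 20% is stated as a share of all managers and rests on pilot data that the article does not show. If the pilot rate was measured over all managers, ineligible ones included, then 20% of 840 could be the right projection even with 690 eligible. This possibility stands, and it makes the 690-based figures conditional. It does not remove the point, because the article draws no such distinction and a reader cannot tell which base applies.

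It is also fair to say that power depends on managers recruited, not on the size of the pool. The inference that the trial is underpowered is therefore not supported: 168 can be reached from 690 if participation is about 24%. Nor do the documents show that the words conservative and minimum are wrong, because the pilot uptake is not given.

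Finally, the likelihood-based model retains all participants and can use 6-week data from managers who drop out later, so a calculation on those followed up may understate power somewhat. The plan's own calculation counts them the same way, so the comparison is like for like. A null result would also be read mainly from its achieved confidence interval. These replies limit the consequence but do not reconcile the counts.

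**Conclusion.** The point holds as an unreconciled conflict between 840 and 690 managers, on which the recruitment target and the power statement depend. The stated figures are right for 840 and not for 690. If 20% participation applies to the 690, expected recruitment falls from 168 to 138 and follow-up from 126 to about 103. Power at 0.54 falls from about 80% to about 72% to 76%, and the effect detectable with 80% power rises from 0.54 to about 0.57 to 0.59.

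This rests on the plan's own drop-out, ICC and alpha, on 1:1 allocation and equal cluster sizes, and on the choice of design effect between 1.07 and 1.15. The loss is moderate. It concerns the forecast and its stated power; randomisation, outcome and analysis are untouched. The document does not show which count is correct.

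**What to change.** Reconcile Participants with Sample size and power calculations to one count of eligible managers, and say which managers the 20% participation rate refers to. If the two counts describe different populations, define both.

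If 690 is the base, choose one of two courses:

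1. Restate the forecast: 16.4 managers per zone, 138 recruited, about 103 followed up, a design effect of about 1.11, and either about 73% to 74% power at 0.54 or 80% power for about 0.58 to 0.59. Change the target in the abstract to match.
2. Keep 168 as the target and state that it needs about 24% participation. The words minimum and conservative should then stay only if the pilot data support that rate.

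If 840 is the base, correct or explain the 690; the power paragraph can then stand. The cost is rewording one paragraph and a sentence in Participants, plus the abstract under the first course, where the stated detectable effect also becomes slightly less favourable.

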## Discussion

This protocol describes a cluster RCT of an online workplace mental health training intervention developed specifically for managers. To the best of our knowledge, this will be the first evaluation of an online intervention that simultaneously addresses how managers can best support and respond to employees experiencing mental health issues, while also promoting primary prevention strategies that may be valuable in creating a mentally healthy workplace for the whole team. Workplace mental health interventions have been found to be effective for particular manager level outcomes such as mental health literacy and mental health promotion behaviours within the workplace [11], as well as improved recognition of and more positive attitudes towards mental health [34]. However, there is limited research with data obtained from both the manager and their direct reports examining the impact of building manager confidence. Data collected for this trial will enable evaluation of outcomes from both managers as well as from employees reporting to them over a four month follow up period.

The dissemination of workplace training via the internet can offer many potential benefits as it offers flexible, yet standardised delivery of educational material, the opportunity for revision of modules, reduced organisational expenses associated with staff attending face-to-face training, and the opportunity to monitor progress through the research platform [20]. However, reduced adherence and low program completion rates are potential problems associated with professional development delivered via eLearning tools. Managers may experience difficulties in prioritising online training sessions due to existing work demands and time pressures compared to a scheduled face-to-face learning session. These factors were taken into consideration when developing *HeadCoach* by designing the program to be easily integrated into a managers’ workload and own learning style. The twelve modules and three topic consolidation exercises are approximately 10 min each in duration. Managers’ may choose to complete one at a time, or to work through as many as they can depending on the time available to them, thus potentially increasing the opportunity for program adherence. Data on program adherence and engagement will be available through the research platform.

A cluster randomisation design has been selected for this RCT. Although this reduces the power of the sample, which has been estimated as capable of detecting a moderate effect size, the method of randomising clusters of managers based on their geographical location reduces the risk of intervention contamination within worksites. However, in the event of substantial movement of managers between work sites, such contamination may be unavoidable. Within the time frame of this study, such movement is unlikely, but demographic data obtained at baseline and follow up will allow the exploration of any organisational movement.

It is also recognised that assigning worksites to the waitlist control condition may also produce some problems. Level of interest and motivation to participate in the trial may wane over time for those in the waitlist control as a result of the delay in being accorded access to the program, and dropout rates have the potential to be higher in the waitlist control group, as incentive to respond to follow up questionnaires may be reduced.

A further potential limitation is the selection of a primary outcome based on self-report, particularly as confidence levels may be prone to a social desirability bias. Although confidentiality of data from participants’ employer is assured, some participants may still hold concerns that could influence their choice to respond, or bias their responses towards more favourable reporting of their level of confidence in the performance of certain managerial behaviours.

Given managers can play a key role in promoting the mental health and well-being of their staff, but that they often report uncertainty about how to best address these matters, it is critical that managers are upskilled and educated, through the latest evidence-based information, in how they can best identify and support the mental health needs of their staff. If effective, the *HeadCoach* online program may provide a practical and efficient method of training a large number of managers in best workplace mental health practices.

